**Fig 5 pone.0315148.g005:**
[figure not shown]
Description of the intervention as an example of personal care activity - organize the week’s medication. D, dominant; DUL, dominant upper limb; ND, non-dominant; NDUL, non-dominant upper limb.

The activity of hanging clothes on a clothesline (Fig 6) is a domestic task, categorized under productivity according to the COPM, and involves various actions, both unilateral (using clothespins) and bilateral (grabbing and hanging clothes). We can select clothespins of different sizes, materials, and resistances, which require more dexterity in the pinch grip, as well as position the clothesline at varying heights to alter the range of motion in the shoulder and elbow along with different types of clothing.

**Fig 6 pone.0315148.g006:**
[figure not shown]
Description of the intervention as an example of productivity activity - hang the clothes on the clothesline. D, dominant; DUL, dominant upper limb; ND, non-dominant; NDUL, non-dominant upper limb.

The activity of playing cards with a deck (Fig 7) is a calm recreational activity, falling under the area of leisure according to the COPM. In the AO intervention session, even while using the same video, we can introduce some variations in how the activity is performed, depending on the individual’s condition and the expected difficulty of the task. For example, we can ask the participant to distribute the cards as quickly as possible, encouraging speed of movement.

**Fig 7 pone.0315148.g007:**
[figure not shown]
Description of the intervention as an example of a leisure activity - shuffle and deal the cards. D, dominant; DUL, dominant upper limb; ND, non-dominant; NDUL, non-dominant upper limb.

In the AO intervention session, we can use the entire video (see supplementary material – S1, S2, and S3 Videos) or select specific stages, based on the person’s motor condition and the expected difficulty of completing the activity. The videos are recorded from a frontal view, in the third person perspective, with the participant’s dominant side being the right side. It can be observed in the activities previously described in the verbal commands that at some points the request for action is to be performed with the dominant hand and at other times with the non-dominant hand. However, during the intervention, the therapist may modify which hand will perform the action, and instead of referring to the dominant and non-dominant hands, they may use the terms right hand and left hand according to the participant’s dominance.

All participants will be advised to maintain their activities but not to initiate any treatment or engage in any form of exercise or sport during their participation in the study. Participants are advised to be in the “on” state of their medication for evaluation and intervention. The established criterion for discontinuing the interventions assigned to a particular participant in the study will be solely at the request of the participant if they no longer wish to participate or if they do not follow the guidance to maintain their activities. To improve participant adherence to intervention protocols, participants will be contacted by telephone to confirm participation in intervention sessions and, at the end of their participation in the study, each participant will receive a written feedback report of the results from the assessments conducted during the tests.

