## Methods

### Study design

This is a description of a protocol for a simple blinded randomized clinical trial to evaluate the effects of the application of MI, AO, and BMI, either individually or in combination, on motor alterations in the UL of individuals with PD. All participants will be evaluated pre-intervention (T0) and post-intervention (T1), and will undergo a follow-up (T2) four weeks after the end of the intervention.

The clinical trial was designed following the Consolidated Standards of Reporting Trials (CONSORT) [16]. The protocol follows the item definitions for clinical trials as per the Standard Protocol Items: Recommendations for Interventional Trials - SPIRIT [17] (S1 Checklist).

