### Ethical aspects

The study is registered on clinicaltrials.gov with the study ID number: NCT05696925 (S3 File). The project was approved by the Research Ethics Committee of the Federal University of Health Sciences of Porto Alegre (UFCSPA), under letter nº 5.638.729, and received the Certificate of Ethical Appreciation Presentation (CAAE) number 61710822.0.0000.5345 (S1 File and S2 File).

To be included, volunteers must read and sign the Informed Consent Form. The entire research was written following Resolution 466/2012 of the Brazilian National Board of Health, and adhered to the principles of the Declaration of Helsinki for research involving human subjects. Data will be processed in accordance with the General Data Protection Law (Brazilian Law nº 13.709/2018).

All researchers are aware of and agree to maintain the confidentiality of personal information about participants that will be collected, shared, and maintained before, during, and after the trial, having signed the Confidentiality Agreement submitted along with the UFCSPA Ethics Committee, and access to the final dataset of the trial will be limited solely to the researchers.

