#### Exclusion criteria.

Having additional central nervous system disorders or other conditions that could affect upper and lower limb function; having other uncontrolled chronic conditions that may interfere with participant safety; and not be using deep brain stimulation (DBS) devices.

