**Fig 3 pone.0315148.g003:**
[figure not shown]
BMI equipment system.

An exoskeleton will be attached to the more affected UL using Velcro straps on the forearm (1), wrist (1), and fingers (5). The participant will be instructed to keep their eyes closed, with their arm in flexion and abduction, elbow flexed at 90°, forearm pronated, wrist in a neutral position, and the hand with the exoskeleton resting on a cushion.

Each of the 10 intervention sessions will consist of 10 exercises with 5 repetitions (including the blocks “relax,” “prepare,” “think,” and “move”), with the 5 chosen tasks imagined twice. Each exercise will last 2 minutes, with a 30-second break between them for the participant to rest. The approximate duration of this stage will be 30 minutes. During each repetition, the participant will listen to four audio commands from the software system: “relax,” “prepare,” “think,” and “move.” When hearing “Relax”, the participant should think of nothing; during “Prepare” and “Think”, the participant will imagine the action, and during “Move”, the exoskeleton will automatically open and close the participant’s hand.

In the “relax” block, the software will quantitatively display this state on the computer screen through a feedback bar, indicating the absence of thought (a clear mind). In the “prepare” and “think” blocks, if the participant can maintain thought for at least 3 seconds (the established time window to avoid false positives) and achieve a score of 70 points (the minimum threshold shown on the feedback bar), the exoskeleton will move (opening and closing the participant’s hand), indicating that the system has detected continuous activation in the primary motor cortex, premotor cortex, or primary somatosensory cortex.

At the end of each exercise, performance will be verified through a graph provided by the system, displaying the score of the achieved degree of imagined movement alongside the most activated brain areas mentioned earlier. Upon completing the 10 intervention sessions, the system will display a graph showing the average degree of imagined movement for each session.

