#### Action execution (AE).

Participants will be instructed to perform the activities as imagined and observed, which can be done while seated or standing. They will be encouraged to execute the activities as they are able, with some activities prompting them to perform as quickly as possible or to alternate hand dominance based on motor symptom manifestation, especially in unilateral activities. Each execution session will also last approximately 2 minutes.

Below are presented the applicability sequences of each intervention group according to their respective approaches (Fig 4).

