**Fig 4 pone.0315148.g004:**
[figure not shown]
Sequence of applicability of interventions. AO, action observation; BMI, brain machine interface; AE, action execution; EG, experimental group; MI, motor imagery.

During the intervention sessions, the difficulty of tasks may be adjusted as the participant progresses in execution, by altering the objects used in the activities, such as sizes, weights, resistances, and different shapes, to change the types of grips and pinches, as well as the range of motion, in addition to being prompted to perform as quickly as possible to stimulate movement speed. It is crucial that the environment is free from distractions to promote concentration during the sessions. Additionally, to ensure proper EEG recording, participants will be advised not to attend sessions with wet hair.

After the intervention period, each participant will undergo the second data collection phase, the post-test (T1), which will take place the day after completing the 10 intervention sessions. This phase will involve the administration of the same four evaluation instruments applied at T0, along with the 9HPT. On this day, participants will also be reminded of the third data collection phase, the follow-up (T2), scheduled to occur four weeks after the conclusion of the interventions. In the follow-up, participants will receive a call and will again respond to the COPM, reporting their satisfaction and performance regarding the problem activities, as well as completing a questionnaire on their perception of the severity of motor and cognitive functions (S1 Graphycal abstract).

Below are some sequences of images as examples of activities recorded on video for the AO. Three activities will be described, each involving an area of occupational performance: self-care, productivity, and leisure, detailed with technical descriptions of the executed movements and a narrative manner involving verbal commands for MI. Here are the examples:

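### As worded, the discontinuation rule is closed to two grounds and leaves out a stop by staff for safety

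*Protocol article*

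**What the plan says.** The rule stands in the closing paragraph of Methods, Interventions, after the card-playing example (Fig 7). It reads "The established criterion for discontinuing the interventions assigned to a particular participant in the study will be solely at the request of the participant" and goes on "if they no longer wish to participate or if they do not follow the guidance to maintain their activities". The guidance meant is given earlier in the same paragraph: participants keep up their usual activities but start no new treatment, exercise or sport during the study.

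The other text that could bear on stopping for safety is this:

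- Exclusion criteria bars people "having other uncontrolled chronic conditions that may interfere with participant safety".
- Ethical aspects says that the research followed Brazilian Resolution 466/2012 and "adhered to the principles of the Declaration of Helsinki for research involving human subjects".
- Interventions allows task difficulty to be adjusted as the participant progresses.
- Protocol amendments sets the route for changes: a formal amendment, submitted to the ethics committee and the trial registry.

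**The concern.** Study design says that the protocol follows SPIRIT, so a reader will take this sentence as the trial's discontinuation rule. It is presented as the established criterion and limited by 'solely'. Read that way, it lets staff end the intervention for someone who takes up a new sport, but not for someone who develops hand pain or unsteadiness and wishes to carry on. Staff who stop such a participant depart from the written rule. Staff who keep to the rule find no safety ground in it.

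What is at stake is participant protection and a clear rule. No effect on power, on the sample size or on the TEMPA analysis is claimed.

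**Working it through.** The question is one of wording, so the check is a reading of the rule against the rest of the article. The counts at the end show scope only.

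**1. What the rule permits.** The natural reading gives two grounds: (i) the participant no longer wishes to take part; (ii) the participant does not follow the activity guidance. Ground (ii) is not a participant request, so it already sits badly with 'solely at the request'. A narrower parse would make ground (ii) depend on a request as well, which makes little sense. On either parse, a stop by staff for an adverse event or a new safety condition is not included.

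**2. Whether another section supplies it.**

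| Place in the Protocol article | What it governs | Safety stop by staff? |
|---|---|---|
| Exclusion criteria | Entry to the trial | No |
| Ethical aspects | General ethical commitments | No stopping rule stated |
| MI via brain-machine interface | Session content, with 30-second breaks | No |
| Action execution | How tasks are done | No |
| Interventions, task difficulty | Progression of tasks | No; adjusts, does not stop |

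The exclusion criterion is the only place in the text shown where participant safety is named, and it works at screening.

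**3. Whether a safety stop is conceivable.** The Introduction lists postural instability among the manifestations of the disease, and participants are at Hoehn and Yahr stages 1 to 3. Action execution describes tasks "which can be done while seated or standing", some of them prompted to be done as fast as possible. In GE4 and GE5 an exoskeleton strapped to the forearm, wrist and fingers opens and closes the hand. Against that, the content is imagery, videos, everyday tasks in bouts of about 2 minutes and passive hand movement, in 10 sessions over two weeks. A need to stop is plausible but probably uncommon.

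**4. Scope.** Inputs: 5 groups of 19 (Sample size), and "Each of the 10 intervention sessions will consist of 10 exercises with 5 repetitions" (MI via brain-machine interface).

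- Participants under the rule: 5 × 19 = 95.
- Planned for the exoskeleton arms: 2 × 19 = 38, and 38 / 95 = 40%.
- Planned repetitions per participant in those arms: 10 sessions × 10 exercises × 5 repetitions = 500, a ceiling.

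These are counts of exposure and measure no harm. The article gives no adverse-event or safety-stop rate, so no expected number of affected participants can be computed.

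**The case against.** The strongest reply is that the finding hangs on one adverb that its own sentence defeats: ground (ii) is not a request, so 'solely' cannot carry its strict meaning. The drafting is loose elsewhere too. Outcome expects a decrease in execution speed where the Abstract speaks of reduced execution time. One stray word is weak evidence that the sponsor meant to bar safety stops. This stands as a point about intent, and staff would very likely stop for safety in practice. It does not rescue the text: if practice would depart from the rule, the rule is what needs correcting.

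A second reply is that adverse-event handling belongs to the full ethics-approved project, which is not shown. This also stands. A reader might infer that the trial has no safety-stop procedure; the article cannot support that. But the article did not stay silent. It stated a rule and closed it. If the project holds a safety stop, the published sentence contradicts it; if not, the gap is real. The sentence needs correcting either way.

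A third reply concerns consequences. A reader might infer that staff may act only when a participant asks to leave. That goes too far: ground (ii) needs no request. Nor does the rule forbid pausing, easing or adapting a session, since it governs discontinuation only. What staff lack in the text is a safety ground for ending the intervention.

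**Conclusion.** The point holds as a defect of wording. The stated rule limits discontinuation to the participant's wish or a breach of the activity guidance, so it excludes a staff stop for an adverse event or a newly arising safety condition, and nothing else in the article supplies that ground.

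Its weight is minor but safety-relevant. The interventions look low risk, the number affected is unknown and may be very small, and the primary analysis is untouched. A reader might take the 40% in the exoskeleton arms or the 500 repetitions as a measure of harm; with no event rate they are not.

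The conclusion assumes that the sentence is meant as the trial's full discontinuation rule, as its wording says. It does not depend on whether adverse-event procedures exist in documents not shown.

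**What to change.** Delete 'solely' and replace the sentence with:

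> The assigned intervention may be stopped (a) at the participant's request, (b) by the investigator or therapist for an adverse event or a newly arising safety condition, or (c) for not following the guidance to maintain activities.

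The clinical threshold for (b) is the sponsor's to set. Ground (b) should not refer back to the exclusion criteria, because the deep brain stimulation item there is itself ambiguously worded.

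The cost is a short amendment under Protocol amendments, to the ethics committee and the registry, with no extra visits, staff or participants. The drawback is timing: recruitment began in February 2023, so the wording applies only from the amendment date, which the report should state.

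A separate, optional addition would be to assess participants who stop early at T1 and T2 where they agree. This would be a new rule, not a clarification: Interventions sets T1 for the day after the 10 sessions are completed, so someone who stops early has no defined T1 date.

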### Outcome

As the main outcome of the study, an improvement in the TEMPA score is expected, along with a decrease in the execution speed of tasks, indicating that participants experienced positive impacts on upper limb motor symptoms after interventions involving action observation, motor imagery, and brain-machine interface. As for secondary outcomes, improvements in motor symptoms are anticipated, evidenced by lower scores on the UPDRS-III and reduced time in the 9 Hole-Peg Test, as well as enhancements in cognitive symptoms indicated by increased scores on the PD-CRS. Additionally, it is expected that the interventions will also have a positive effect on occupational performance, leading to better performance and satisfaction in daily activities as assessed by the COPM. The averages of the assessments will be considered, with measurements for each outcome taken at T0 and T1, and at T2 regarding perceptions of changes in motor and cognitive conditions, as well as the COPM.

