**Expected results:**

The primary outcome expected is an improvement in the Test d’Évaluation des Membres Supérieurs de Personnes Âgées score, accompanied by a reduction in task execution time. Secondary outcomes include motor symptoms in the upper limbs, assessed via the Unified Parkinson’s Disease Rating Scale - Part III and the 9-Hole Peg Test; cognitive function, assessed with the PD Cognitive Rating Scale; and occupational performance, assessed with the Canadian Occupational Performance Measure.

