### Randomization, allocation and blinding

Following selection, participants will be randomly allocated into one of five experimental groups: GE1 (motor imagery, action observation, and action execution), GE2 (motor imagery and action execution), GE3 (action observation and action execution), GE4 (motor imagery via brain-machine interface and action execution), and GE5 (motor imagery via brain-machine interface, action observation, and action execution) (Fig 2).

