### Data collection

The following instruments will be used for pre-intervention (T0) and post-intervention (T1) assessments. The Test d’Évaluation des Membres Supérieurs de Personnes Âgées (TEMPA) will be employed to evaluate limitations of the UL through tasks that simulate activities of daily living [23]. The final score of the test, which can reach up to 186 points, corresponds to the sum of the functional score, encompassing unilateral and bilateral tasks (totaling up to 36 points), and the task analysis score, which assesses five areas of sensory and motor skills in the UL (totaling up to 150 points). In this study, unilateral tasks will be performed using the more affected UL. For better interpretation, especially in task analysis, sessions will be recorded for subsequent analysis.

To assess fine manual motor performance, the 9-Hole Peg Test (9HPT) will be administered, considering the average times based on sex and manual dominance: for men, 21.1 seconds for the dominant hand and 22.3 seconds for the non-dominant hand; for women, 19.9 seconds for the dominant hand and 21.4 seconds for the non-dominant hand [22]. This instrument will be used as a screening tool, and data from included participants will be analyzed in the final results.

To evaluate motor disturbances in PD, the Unified Parkinson’s Disease Rating Scale - part III (UPDRS-III) will be utilized, which involves motor assessment [24], excluding items related to facial symptoms or those corresponding to motor symptoms in the lower limbs. The maximum score is 32 points, with higher scores indicating worse symptoms.

Cognitive functions will be assessed using the Parkinson´s disease -Cognitive Rating Scale (PD-CRS), which encompasses nine functions: sustained attention, working memory, immediate and delayed verbal memory recall, alternating verbal fluency, action verbal fluency, spontaneous clock drawing, visual confrontation naming, and clock drawing copying. The total score for the PD-CRS is 134 points [25].

The Canadian Occupational Performance Measure (COPM) is a semi-structured interview that identifies problem activities in the areas of self-care, productivity, and leisure. For this study, participants will choose up to five problem activities, rating them from 1 to 10 based on their performance and satisfaction [26]. In cases of motor symptoms in the non-dominant UL, participants will be instructed to select problem activities that involve more bimanual actions.

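### The main outcome is worded as a pre-post TEMPA gain showing benefit, but every arm is active, so only between-arm differences in change can be attributed to MI, AO or BMI; the same sentence also reverses the direction of execution speed

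*Protocol article*

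**What the plan says.** **Main outcome.** The Outcome section states that "an improvement in the TEMPA score is expected, along with a decrease in the execution speed of tasks, indicating that participants experienced positive impacts" on upper-limb symptoms "after interventions involving action observation, motor imagery, and brain-machine interface". No between-group contrast appears in that sentence. The abstract (Expected results) gives the second element as "accompanied by a reduction in task execution time".

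**Arms.** Under Randomization, allocation and blinding, "participants will be randomly allocated into one of five experimental groups". Each of GE1 to GE5 combines action execution (AE) with motor imagery (MI), action observation (AO), MI through the brain-machine interface (BMI), or a combination of these. No arm is AE-only, sham, usual care or untreated. Every arm has ten sessions of about 60 minutes (Interventions).

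**TEMPA.** Data collection says that the final score "corresponds to the sum of the functional score, encompassing unilateral and bilateral tasks (totaling up to 36 points), and the task analysis score" (up to 150 points), giving a maximum of 186. Execution time is not a component.

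**Sizing and analysis.** Sample size names TEMPA alone as primary and powers the time-by-intervention interaction. Statistical analysis plans tests of group, time and their interaction.

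**9HPT.** Eligibility requires a slower-than-average 9-Hole Peg Test time. Data collection adds: "This instrument will be used as a screening tool, and data from included participants will be analyzed in the final results". Interventions schedules four instruments at T0 and, at T1, "administration of the same four evaluation instruments applied at T0, along with the 9HPT".

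**The concern.** The stated outcome reads a before-after change as evidence that the techniques worked. With no arm free of them, such a change could equally come from executing the tasks, from taking TEMPA twice about two weeks apart, or from therapist attention. The analysis plan includes a test of the time main effect, so a result that appears to confirm the outcome sentence will be produced whatever its cause. At stake is the trial's headline claim: a report could say that AO, MI and BMI have positive effects when the design can show only whether one active package does better than another.

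The sentence has two further faults. It expects execution speed to fall, which is slowing. It also sets execution time beside the score without saying how the two relate.

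**Working it through.** **1. The plan's own figure.** Inputs from Sample size: f = 0.2, k = 5 groups, m = 2 assessments, alpha 0.05, power 80%, attrition margin 19%, total 95. The article gives no correlation between assessments; rho = 0.5 is assumed.

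- Interaction test: noncentrality = f² × N × m / (1 − rho), with df (k − 1)(m − 1) = 4 and (N − k)(m − 1).
- At N = 80: 0.04 × 80 × 2 / 0.5 = 12.8, df 4 and 75, power 0.803. N = 80 is the smallest total that reaches 80%.
- 80 × 1.19 = 95.2, which matches the stated 95 (19 per group).
- Sensitivity to rho, before attrition: N = 155, 110, 80, 50 and 35 for rho = 0, 0.3, 0.5, 0.7 and 0.8.

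The stated total therefore belongs to a between-arm comparison of change on TEMPA, not to the pre-post improvement described under Outcome.

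**2. What a change common to all arms would produce.** Suppose all five arms shift by the same amount d (in raw SD) and no technique adds anything. SD of change = √(2(1 − rho)) = 1 raw SD at rho = 0.5. The time main effect then has noncentrality N × d², with df 1 and N − 5.

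| Common shift d (assumed) | N × d² at N = 80 | P(time effect significant), N = 80 | Same, N = 95 |
|---|---|---|---|
| 0.2 SD | 3.2 | 0.42 | 0.49 |
| 0.3 SD | 7.2 | 0.75 | 0.82 |
| 0.4 SD | 12.8 | 0.94 | 0.97 |

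Under the same supposition the interaction is significant only at its nominal 0.05. The documents give no practice or retest effect, so the range matters more than any single row.

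**3. Direction.** Outcome expects speed to decrease. The abstract expects time to decrease, which means that speed increases. Interventions has participants "perform as quickly as possible to stimulate movement speed". Two places agree that faster is better; the Outcome sentence says the reverse.

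**4. Two quantities.** 36 + 150 = 186 leaves no room for time in the TEMPA total. Score and time are separate quantities, and Sample size covers only what it calls TEMPA.

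**5. 9HPT baseline.** Data collection lists the 9HPT among the instruments for T0 and T1, and Outcome says that each outcome is measured at both. Interventions counts four instruments at T0 and adds the 9HPT at T1, which suggests that the screening value serves as baseline. If it does, selection on that value gives regression to the mean of (1 − r) × φ(c)/Φ(c), in SD of the screened population, where r is retest reliability and the cutoff lies c SD below the screened mean. Both are assumed:

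- c = 0: 0.798 × 0.2 = 0.16 (r = 0.8); 0.798 × 0.1 = 0.08 (r = 0.9)
- c = 1: 0.288 × 0.2 = 0.058 (r = 0.8); 0.288 × 0.1 = 0.029 (r = 0.9)

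Some apparent improvement, about 0.03 to 0.16 SD, would then arise from selection alone. It is expected to be equal across randomised arms.

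**The case against.** The strongest reply is that the plan already does the right test. Sample size names one primary outcome and powers the interaction; Statistical analysis tests it, with Sidak-adjusted comparisons. The Outcome sentence describes what is expected and sets no success rule, and the conclusion of the Discussion leaves effectiveness to future trials. Active-comparator designs are legitimate, and the study design section explains the aim as techniques applied singly or together, which contrasts among these arms partly address. All of this stands. It confines the defect to the stated outcome and the inference drawn from it. It does not make that inference sound, because the sentence still reads improvement over time as impact of the techniques.

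Several stronger readings are tempting but unsupported:

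- *That the trial has no comparator.* It has no inactive or AE-only arm, but its randomised contrasts between active arms are valid.
- *That ten hours of task practice explain any gain.* Ten hours is total session time. Execution is only part of it; the BMI stage alone takes about 30 minutes of a session.
- *That two primary quantities raise the false-positive rate to 1 − 0.95² = 9.75%.* That needs success on either quantity and independent tests. The text joins score and speed as occurring together, and both come from the same TEMPA tasks.
- *That the 9HPT is certainly not measured at T0.* The sections disagree, and the schedule figure, which might settle it, is not shown in the copy reviewed.

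**Conclusion.** The point holds as a fault in how the main outcome and its interpretation are stated. The sample-size arithmetic reproduces (with rho = 0.5 assumed), and the planned interaction test is appropriate. The pre-post reading is unsafe: a common shift of 0.2 to 0.4 SD unrelated to the techniques would give a significant time effect with probability of about 0.42 to 0.94 at N = 80. Those figures rest on the assumed shift and on an SD of change of 1 SD. A reader might infer that a null trial would almost surely appear positive; that is true only towards the upper end of the range, and at 0.2 SD it is less likely than not.

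The reversed direction and the added quantity are plain inconsistencies. The 9HPT issue is a small, conditional one on a secondary outcome.

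**What to change.** - **Primary endpoint.** State it as the between-arm difference in T0-T1 change in TEMPA total score, tested by the group-by-time interaction.
- **Within-arm change and the time main effect.** Label both as descriptive, and not as evidence that MI, AO or BMI works.
- **Objective and conclusions.** Limit them to incremental effects: GE1 vs GE2 (AO added to MI), GE1 vs GE3 (MI added to AO), GE4 vs GE2 (BMI-guided vs therapist-guided MI), GE5 vs GE4 (AO added to BMI-guided MI) and GE5 vs GE1 (BMI-guided vs therapist-guided MI, both with AO).
- **Execution time.** Change speed to time in the Outcome section, with lower as better, and make it a secondary endpoint.
- **9HPT.** Reconcile Data collection and Outcome with the two counts of instruments in Interventions. If the screening value is the baseline, interpret only between-arm differences.

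The cost is a wording amendment through the route in Protocol amendments, with no extra participants or visits. Data collection and analysis are expected to run to September 2026. The price is a more modest claim. The individual contrasts are valid but imprecise: with 16 per arm and a 0.4 SD difference in change (SD of change 1 SD), noncentrality is 0.4 × √(16/2) = 1.13 and unadjusted two-sided power is about 0.19. They should be reported with confidence intervals and read accordingly.
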